### Oversight and monitoring

#### Composition of the coordinating center and trial steering committee {5d}

This single-site randomized trial does not have a coordinating center or trial steering committee. The trial will be supervised by the PI (VC) with input from study co-investigators (co-authors EM, DB, PM, and ZP). Additional oversight will be provided by an independent Safety Officer who will review study conduct and progress on an annual basis as outlined in our NIH-approved Data and Safety Monitoring Plan (DSMP). Two senior-level Professional Research Assistants (PRAs, co-authors KB and LW), supervised by the PI, will provide day-to-day organizational support for the trial including participant recruitment and obtaining informed consent and will oversee other study staff (PRAs and/or student workers) in scheduling and performance of outcome measures and data entry. The screening medical history and physical exams will be performed by the PI (VC), co-investigator (DB), and co-author (AZ), all of whom are MDs with current board certification. The PI and the study PRAs will meet weekly to discuss trial conduct and progress including recruitment and retention. Co-investigator meetings will be held monthly during the study startup phase and then as needed to discuss any issues that arise with trial conduct.

#### Composition of the data monitoring committee, its role, and reporting structure {21a}

The intervention and measurement protocols pose minimal risk to participants. Because of this low-risk status, the data safety monitoring plan for this trial focuses on close monitoring by the principal investigator (an MD with current board certification in Endocrinology) in conjunction with an independent Safety Officer, along with prompt reporting of excessive adverse events and any serious adverse events to the NIH and to COMIRB. The Safety Officer will review the reports prepared by the study coordinator at the annual Safety Officer meeting and will determine whether there is any corrective action, trigger of an ad hoc review, or stopping rule violation that should be communicated to the study investigator, COMIRB and the study sponsor.

#### Adverse event reporting and harms {22}

We plan to collect adverse event data on a case-by-case basis. Adverse events will be reviewed, collated, and evaluated by the PI within 72 h. All serious adverse events will be evaluated by the Safety Officer and the PI within 24 h. A summary table of adverse events (Safety Report) will be compiled on an ongoing basis and will be provided to the independent safety officer at the annual meeting. The summary table will include a description of the adverse event, the date of onset, severity, action taken, outcome, whether the adverse event was expected or unanticipated, and a determination of the relationship of the adverse event to study procedures. Adverse event reports and annual summaries will not include identifiable material and participants will be identified only by study ID number.

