#### Strategies to improve adherence to interventions {11c}

#### Group-based behavioral support

To improve adherence to the interventions, both groups will receive a 52-week group-based behavioral weight loss program with equivalent contact and support (see Table 2 for a list of weekly behavioral support topics). The programs will fulfill all recommendations for behavioral interventions for treatment of obesity outlined in current guidelines [17]. Randomized groups will meet separately. Curriculum for DCR will be based on the Colorado Weigh behavioral weight loss program which was developed at CU-AMC in 2000 and uses a skills-based approach and cognitive behavioral strategies for lifestyle modification with a dietary focus on DCR [44, 45]. Curriculum for IMF will also be based on the Colorado Weigh behavioral weight loss program and features similar weekly curriculum themes as used in DCR but adapted by the study PI (VC) with input from a registered dietitian (KB) and a behavioral psychologist (AC) to focus on behavioral support specific to IMF. Group meetings will be taught by a registered dietitian with experience in leading group-based behavioral weight loss interventions. Groups will meet weekly during weeks 0–13 and every 2 weeks during weeks 14–52. Weight will be obtained at each group meeting. Group sessions will last ~60 min and the curriculum will be delivered using a mix of large group discussion, small breakout discussions, visual demonstrations, and written exercises. Participants in the IMF group will be instructed in specific strategies to support IMF including strategies to deal with hunger on fast days, distraction techniques, and choosing a balanced diet/appropriate portions on fed days. Participants in the DCR group will be instructed in specific strategies to support DCR with a focus on daily calorie counting and food logging. Topics covered in both groups during the first 26 weeks include realistic weight loss goal setting, self-monitoring strategies, mindful eating, stress management, cognitive restructuring, improving personal food environments and social networks, and strategies to overcome barriers to healthy eating and increasing PA. Later in the curriculum (weeks 27–52), topics will focus on strategies for weight loss maintenance and include impact of weight loss on EE and propensity for weight regain, relapse prevention, and identifying motivation for long-term dietary and PA changes. Participants will also be provided two 10–15 min 1:1 phone calls with their group leader during the initial 26 weeks of the intervention for individualized dietary goal setting using a standardized protocol.

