#### Criteria for discontinuing or modifying allocated interventions {11b}

Participants will not be withdrawn for non-adherence in this intent-to-treat study. Participants in both groups will be encouraged to adhere to the dietary prescriptions without modification for the initial 2 weeks as a prior study suggests individuals with obesity become habituated to IMF after ~2 weeks [38]. After the initial 2 weeks, a standardized dietary modification will be offered if a participant (1) expresses a desire to withdraw due to intolerance of study diet and/or (2) experiences adverse effects related to the study diet (i.e., insomnia, impaired concentration, headaches, irritability) that impair ability to function. DCR participants will be allowed to raise their calorie goal to target an energy deficit of 20% from weight maintenance requirements. IMF participants will be allowed to reduce fasting to 2 days per week (i.e., reduce targeted weekly energy deficit to ~20%). Participants will be allowed to continue these strategies for 2 weeks and will then be asked to re-try the original dietary prescription. If they are still unable to tolerate the original dietary prescription after a second attempt, they will be allowed to continue at the modified levels for the study duration. Percentage of participants in each group requiring sustained intervention modification will be recorded. The allocated interventions will not be modified other than as described above. However, participants may discontinue the intervention and/or choose to withdraw from the study at any time.

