#### Self-reported dietary adherence, effort, and self-efficacy

Self-reported dietary adherence and ratings of effort to adhere to the prescribed study diets will be obtained on a monthly basis during weeks 1–52 using methodology described by Dansinger et al. [2]. Participants will be asked to rate on a 1–10 Likert scale: (1) how adherent they were to the prescribed study diet over the past week, (2) how hard was it to adhere to the prescribed study diet over the past week, and (3) how likely they feel they can adhere to the prescribed diet for the next month. Participants in the IMF group will be asked to report the number of fast days over the past week. During weeks 53–78, monthly dietary follow-up questionnaires will be administered to evaluate participant efforts to continue weight loss or weight maintenance after the 52-week intervention has ended.

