### Assignment of interventions: blinding

#### Who will be blinded {17a}

Due to the nature of the intervention, it is not plausible to blind participants. However, participants will be blinded to the study hypothesis. Due to the nature of the group-based behavioral intervention, it is also not plausible to blind study staff who enroll participants and deliver or monitor intervention delivery. However, the following personnel will be blinded to study group assignment: (1) staff performing laboratory analyses, (2) DLW assessment core staff performing analysis of the DLW samples, and (3) Colorado Clinical and Translational Sciences Institute Nutrition Core personnel who will be using Nutrition Data System for Research software to analyze the 7-day diet diary data. Lastly, all data analyses and reporting will be completed by study investigators who are blinded to study arm assignments.

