### Statistical methods

#### Statistical methods for primary and secondary outcomes {20a}

Baseline characteristics will be summarized by treatment groups using descriptive statistics. Normality assumptions will be evaluated, and transformations used (e.g., square root and log) as appropriate. Body weight is the primary outcome variable and others are secondary or exploratory outcomes. Consequently, no adjustment for multiple outcomes will be applied. *P*-values < 0.05 will be considered significant. Any imbalance in baseline characteristics between groups that could potentially be a confounding factor for the outcome will be adjusted for in the statistical model.

The primary analysis will use the “intent-to-treat” principle and all randomized participants will be analyzed. Each continuous outcome will be analyzed using a linear mixed effects model. The fixed effects of the linear mixed effects model will consist of treatment group (IMF or DCR) and time of measurement (i.e., baseline and follow-up time points) and their interaction. Time of measurement will be treated as a continuous or categorical variable, as appropriate. Test of the interaction assesses the difference in post-intervention change from baseline between two groups and is used to quantify the effectiveness of the intervention. The 90% confidence interval for the interaction will be calculated. Incidence of adverse events, protocol modifications, and attrition will be compared between groups using chi square or Fisher’s exact test as appropriate.

To explore the impact of selected biologic, psychosocial, behavioral, and/or environmental variables on the intervention effect, we will initially apply models similar to those being tested in aim 1, with the addition of a potential effect moderator as a covariate and its interaction term (i.e., intervention × moderator × time interaction) in addition to related two-way interaction terms. Among factors with a significant three-level interaction, we will further use post-intervention weight loss as the outcome and multiple linear regression to examine their association with the outcome and its interaction with intervention. Similar multiple logistic regression analysis will also be conducted with the outcome dichotomized as responder and non-responder using clinical criteria.

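### Adverse events are collected case by case with no common question or schedule described, yet their incidence is formally tested between two unblinded arms, so differential reporting cannot be excluded

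*Protocol article*

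**What the plan says.** Four parts of the protocol article bear on this.

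- **Collection.** Adverse event reporting and harms {22}: "We plan to collect adverse event data on a case-by-case basis". The section then covers what follows once an event is known: review by the principal investigator within 72 h, evaluation of serious events within 24 h, and the fields of the summary table. It names no standard question, no collection times, no collector and no setting.
- **Analysis.** Statistical methods {20a}: "Incidence of adverse events, protocol modifications, and attrition will be compared between groups using chi square or Fisher’s exact test as appropriate".
- **Blinding and setting.** Section {17a}: "Due to the nature of the intervention, it is not plausible to blind participants", and "it is also not plausible to blind study staff who enroll participants and deliver or monitor intervention delivery". Under Group-based behavioral support: "Randomized groups will meet separately". The same section says "both groups will receive a 52-week group-based behavioral weight loss program with equivalent contact and support".
- **Diet modifications.** Section {11b} allows a two-week easing of the diet in either arm for intolerance or diet-related adverse effects, followed by a retry. It then says: "Percentage of participants in each group requiring sustained intervention modification will be recorded".

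Both arms already share regular contacts. Clinic visits fall at baseline and weeks 13, 26, 39 and 52. There is also a monthly survey: "Self-reported dietary adherence and ratings of effort to adhere to the prescribed study diets will be obtained on a monthly basis during weeks 1–52". As described, its items cover adherence, effort and confidence, and, for the fasting arm, the number of fast days. No symptom item is mentioned.

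**The concern.** A between-arm test of incidence compares harm only if an event has about the same chance of being recorded in each arm. Case-by-case collection, as worded, does nothing to secure that. In a blinded trial, haphazard capture tends to be equally haphazard on both sides. Here participants and intervention staff know the diet. The classes are separate, and only the fasting classes cover coping with hunger on fast days and adjusting exercise around them. Such content could bring symptoms to staff attention, or it could make them seem normal and leave them unreported.

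Tolerability is part of the case for intermittent fasting: the Introduction cites the pilot's finding that it was safe and tolerable, and raises concern about tolerance of a related regimen. A significant difference in adverse events, or the lack of one, would be read as evidence on that question when it might partly reflect how events came to be recorded.

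There is a smaller, related mismatch. Section {11b} commits to recording sustained modifications, while section {20a} compares protocol modifications without saying which kind.

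**Working it through.** **Inputs from the article:** 75 participants per arm (Sample size {14}), significance at 0.05 and a chi-square or Fisher's exact test ({20a}). The article gives no adverse event rate, no capture rate and no power figure for this comparison, so there is no stated figure to reproduce.

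**Assumptions, not from the article:** the same true proportion π of participants with an event in both arms, and capture probabilities c₁ and c₂.

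**Step 1. Observed proportions.** p₁ = π·c₁ and p₂ = π·c₂. With π = 0.40, c₂ = 0.50 and c₁ = 0.65 or 0.80:

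- p₂ = 0.40 × 0.50 = 0.20
- p₁ = 0.40 × 0.65 = 0.26, or 0.40 × 0.80 = 0.32

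With π = 0.30: p₂ = 0.15, and p₁ = 0.195 or 0.24.

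**Step 2. Rejection rate.** Sum the binomial probabilities Bin(i; 75, p₁)·Bin(j; 75, p₂) over all tables (i, j) where the test rejects at 5% two-sided. The Pearson chi-square is used without continuity correction.

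| True π | Capture | Observed | Chi-square rejects | Fisher rejects |
|---|---|---|---|---|
| 0.40 | 50% v 50% | 0.20 v 0.20 | 5.1% | 3.1% |
| 0.40 | 65% v 50% | 0.26 v 0.20 | 13.9% | 10.2% |
| 0.40 | 80% v 50% | 0.32 v 0.20 | 38.7% | 32.3% |
| 0.30 | 65% v 50% | 0.195 v 0.15 | 11.4% | 7.5% |
| 0.30 | 80% v 50% | 0.24 v 0.15 | 28.7% | 21.9% |

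Every rejection is false, because the true rates are equal. The table is symmetric: swapping which arm is captured better changes the direction of the false signal, not its frequency.

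**Step 3. Sensitivity to the assumptions.** With 80% v 60% capture, chi-square rejects in 11%, 19% and 34% of trials at π = 0.20, 0.40 and 0.60. With 90% v 60% the figures are 18%, 36% and 62%. With equal 70% capture they stay at about 5%.

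**Step 4. Masking.** Unequal capture can also hide a real difference. If true rates were 40% and 30% and capture were 60% and 80%, both arms would show 24% (0.40 × 0.60 = 0.30 × 0.80 = 0.24).

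**The case against.** **Opportunity to report is similar by design.** Contact is stated to be equivalent, visit weeks are common, and the adverse-effect route to an eased diet is parallel in both arms. This stands, and it limits how far capture could diverge. But equal contact is not equal questioning, and nowhere does the article say that events are asked about at these contacts.

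**The detail may sit elsewhere.** The article cites a data and safety monitoring plan that is not shown, and how events are elicited could be set out there. This lowers confidence that no structured elicitation exists. The point rests on the method the article does state and on its pairing with a formal test.

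**Stronger readings that the document does not support:**

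- A reader might infer that class staff collect events in the arm-specific classes. The harms section names no collector or setting.
- A reader might infer that spontaneous mention is the sole route by which an event is recorded. The wording is vague and does not say so.
- A reader might infer that the fasting arm's rate will be inflated, or that the comparison measures reporting as much as harm. No capture figure supports either, and coping advice could push reporting either way.
- A reader might infer that temporary diet modifications go unrecorded. Section {11b} does not say that only sustained ones are recorded, and the modify-then-retry procedure implies some tracking.

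**Timing.** Enrollment ended on 4/29/2021. Week-78 measures were expected by 12/19/2022, which puts the last week-52 visits around June 2022, before the article appeared. A checklist during the intervention therefore could not be added for these participants, and the fix needs a fallback.

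**Conclusion.** The point holds in a limited form. The article pairs unstandardised adverse event collection with a significance test between two unblinded, separately taught arms, so differential reporting cannot be excluded. The document does not show that it occurs, which way it would run, or how large it would be.

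Under assumed capture differences of 15–30 points and true incidence of 30–40%, the chi-square false-positive rate would be about 11–39% instead of 5%; Fisher's test is lower (about 7–32%) but still inflated. Other assumptions move the range, and equal capture removes the problem. The consequence is confined to the safety and tolerability comparison.

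On modifications, sections {11b} and {20a} need aligning; this is a matter of clarity, not evidence of lost data.

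**What to change.** 1. **Collection.** Use one short symptom checklist, identical in both arms, at the existing monthly survey and clinic visits. Include at least the effects already named in section {11b} (headaches, irritability, insomnia, impaired concentration) and one open question.
2. **Analysis.** Base the between-arm comparison in section {20a} on these solicited events. List spontaneously reported events separately.
3. **Data already collected case by case.** Report how events were ascertained in each arm. Present counts and percentages descriptively, without a significance test.
4. **Modifications.** State in sections {11b} and {20a} that the protocol modifications compared include both temporary and sustained ones, reported separately.

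The cost is a few items on contacts that already exist and a larger number of minor events to review. For participants who have finished the intervention only items 3 and 4 apply; these cost some reporting text and whatever checking of records item 4 needs.

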#### Frequency and plans for auditing trial conduct {23}

To review study conduct throughout the trial period, study team meetings, led by the PI (VC), will occur on a weekly basis. The independent Safety Officer will review trial conduct and progress annually, as outlined in our NIH-approved DSMP. An annual report will be submitted for continuing review per COMIRB requirements. Lastly, an annual progress report will be submitted to the study sponsor (NIH).

#### Plans for communicating important protocol amendments to relevant parties (e.g., trial participants, ethical committees) {25}

Any protocol changes that impact study procedures or risk to human subjects will be approved by COMIRB and reflected in a revised consent form that will be reviewed and signed by all active participants. Protocol changes will also be reported to NIH at the annual progress reports.

#### Dissemination plans {31a}

Findings from this study will be shared publicly and disseminated mainly by publication in peer-reviewed journals and conference presentations. Journal articles will be submitted to PubMed Central in compliance with NIH access guidelines. Main outcomes are planned to be submitted for publication during 2023–2024. Peer-reviewed findings will also be disseminated through CU-AMC social media outlets. Research data, which documents, supports, and validates research findings, will be made available after the main findings from the final research data set have been accepted for publication. No research data with personal identifiers will be published under this project.

## Discussion

Although weight loss interventions based on DCR lead to modest weight loss success in the short-term, there is wide inter-individual variability in weight loss and poor long-term weight loss maintenance. Evidence-based dietary approaches to energy restriction that are effective long-term are needed to provide a range of evidence-based options to individuals seeking weight loss. IMF may represent a promising dietary strategy to help more people achieve weight loss and improve their metabolic health. A recent systematic review identified 27 IMF trials (published between 7/1/2019 and 1/1/2000) reporting weight loss ranging from 0.8 to 13.0% of baseline weight, with no serious adverse events [16]. However, the current evidence base has significant limitations including lack of a standard-of-care DCR control, failure to provide guideline-based behavioral support, and failure to rigorously evaluate dietary and PA adherence using objective measures. To date, only three longer-term (52-week) trials have evaluated IMF as a weight loss strategy [19–21]. None of these longer-duration studies reported significant differences between IMF and DCR in changes in weight. However, each of these studies has limitations that prohibit drawing generalizable conclusions about the relative long-term efficacy of IMF compared to DCR for obesity treatment. Thus, greater scientific rigor is required from interventional trials than found in the current literature and well-designed trials are needed to demonstrate long-term effectiveness and to understand the impact of IMF on energy balance.

DRIFT will fill this gap in the literature by examining the effectiveness of IMF as a dietary strategy to achieve weight loss compared to DCR, the current standard-of-care, within the context of a 52-week, guideline-based behavioral support program for obesity treatment. We will use objective methods to measure EI (DLW intake-balance method) and PA (activPAL device) to allow for an accurate comparison of adherence to the dietary and PA prescriptions between the IMF and DCR groups. This trial is also unique in that it will be one of the first obesity treatment trials to implement the recommendations from the NIH ADOPT framework to evaluate selected biologic, behavioral, environmental, and psychosocial predictors of weight loss response [24–28]. Our findings may have significant public health implications as this study will generate robust data regarding long-term weight loss effectiveness of IMF as compared to DCR. We anticipate that results will further our understanding of the impact of IMF on energy balance and will provide preliminary insight into predictors of weight loss response within IMF and DCR.

